### Participant timeline

#### Trial baseline

The start of patient inclusion is February 1, 2018, and the study will be finished February 28, 2020. The first results are expected by April 30, 2020.

#### Time Schedule for Measuring Assessing Symptoms As Edema

The time schedule will be as follows:

In the open clinic when the patient is included.The day after the operation.Day 4 and the day of patient discharge.Day 42 (control in our open clinic for control of the operation results).

The measure procedure will be as follows:

The circumference of the leg will be measured at 10 cm below the distal part of the patellae and 8 cm above medial malleolus.In the same procedure, we will evaluate pain by the Visual Analogue Scale (VAS).Randomization when the patient is on the operation table.Operation performed.Post operation.The control group follows the department’s ordinary postoperative routines for inset bypass — short-stretch bandage. A short-stretch bandage is a padded bandage that stretches from the toes and up to the upper thigh with a 40 mmHg pressure.Time for full mobilization is recorded in all patients.Reoperations is noted.Toe pressure is measured at inclusion, immediately post operation and at discharge.Time for discharge is noted.Paraclinical factors to be examined: confusion, pneumonia, infection of the urinary tract.Duplex study at Day 42 of reverse flow in the deep veins associated with standard duplex study of AV fistulas postoperatively.Quality of life questionnaire (VascuQol-6) baseline + 42 days + 6-month + 12-month, (Appendix 1).EQ-5D baseline + 42 days + 6-month + 12-month, (Appendix 2).

### Sample size

The sample will comprise of 50 patients in each group with a total of 100 patients.

### Statistical Analysis and Structural Analysis

Through decreasing the postoperative edema by 50 %, we can reduce the wound complication rate for patients from 18% to 12%, given a sigma of 10 and the two-sided test, with an alpha value of 0.05 and beta of 0.80 involving 44 patients in each group. Assuming a dropout rate of 6 patients in each group, the “sample size” will rise to 50 in each group.

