**Results:**

The primary endpoint is reduction of leg edema by at least 50%. The secondary endpoint includes earlier mobilization in the pump group and decreased length of stay in hospital. Quality of life is evaluated through the European Health Related Quality of Life Questionnaire 5 Dimensions (EQ-5D) and Vascular Quality of Life Questionnaire-6 (VascuQol-6) questionnaires. The start of the study is February 1, 2018, and the end of the study is February 1, 2020. First results will be available April 2020.

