## Introduction

Critical leg ischemia (CLI) is a predominant cause of poor wound healing, leg amputation [1], and has a significant, negative impact on quality of life [2]. In patients with CLI, the standard operative choice is an in situ bypass to the lower extremity to improve the patient's prognosis and quality of life. However, postoperative complications after an in situ bypass occur in 18% of patients, prolonging their hospitalization and convalescence. The main postoperative complication is edema. Measured 10 cm below the patella, edema is developed among approximately 6%-8% during the first day, increasing to 8%-10% at the fourth day (nonpublished). Postoperative edema can be prevented by early mobilization which stimulates the natural venous pump in the leg, but mobilization is often difficult in patients with CLI due to wound problems prior to surgery. In addition, CLI is associated with age and limited walking distance and coexists with other manifest diseases, which might also make mobilization difficult. Supportive stimulation of the venous pump by an impulsive compression foot pump may be an effective solution. Patient’s stimulation of the venous plexus in the arch of the foot has shown to reduce leg edema and thrombosis risk in patients undergoing orthopedic surgery on the lower extremities [3-10]. However, in the literature, there is no description of treatment of vascular surgical patients treated with foot pump. Thus, the primary objective of this study is to investigate whether a foot pump is effective in reducing postoperative edema in patients undergoing an in situ bypass.

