### Outcomes

#### End points

The end points are as follows:

Reduction of leg edema by 50%, 10 cm below the patella and 8 cm proximal of the medial malleolus on the operated leg three days post operation in patients treated with impulsive compression in comparison to nontreated.“Wound complications” are defined according to the national Danish vascular registry “karbase”, including infections, hematoma, and lymph excretion over two days. The pump is expected to have influence on the wounds on the thigh/crus and not in the groin. We therefore separate on wound complications in the groin and the other part of the leg.Time to mobilization in pump treated patients (ie, patient can get out of bed and go to the toilet).Length of stay in hospital.

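### The sample-size paragraph gives no power basis for the primary edema endpoint, and its 80% does not hold for wound complications either

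*Protocol article*

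**What the plan says.** The Abstract (Results) is explicit: "The primary endpoint is reduction of leg edema by at least 50" percent. The Introduction also makes edema reduction the primary objective. The End points section lists edema first, measured 10 cm below the patella and 8 cm proximal to the medial malleolus, "on the operated leg three days post operation in patients treated with impulsive compression in comparison to nontreated". Wound complications come after it in that list.

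The only sample-size reasoning is in Statistical Analysis and Structural Analysis. It starts from edema but puts its numbers on wound complications: "Through decreasing the postoperative edema by 50 %, we can reduce the wound complication rate for patients from 18% to 12" percent, "given a sigma of 10 and the two-sided test", alpha 0.05, and "beta of 0.80 involving 44 patients in each group". Six dropouts per group raise this to 50.

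The only edema magnitudes are in the Introduction: "Measured 10 cm below the patella, edema is developed among approximately 6%-8% during the first day, increasing to 8%-10% at the fourth day", marked there as unpublished. Under Statistical methods, continuous variables are compared by t test or Wilcoxon rank sum test and binary variables by chi-square test.

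**The concern.** A power statement has to refer to the comparison on which the trial will be judged. Here the 50% edema reduction appears only as the presumed route to fewer wound complications, and the effect size is a pair of wound-complication rates. The primary comparison therefore has no stated effect, no SD and no power.

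The same sentence has a second defect. A rate of 18% against 12% is a comparison of two proportions, whose variance follows from the rates themselves. A separate sigma belongs to a comparison of means.

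What is at stake is interpretation. If the edema comparison is not significant, anyone who attaches the 80% to it could take the result as good evidence against a halving of edema. The document gives no ground for that.

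**Working it through.** **Inputs.** From Statistical Analysis and Structural Analysis: 18% and 12%, sigma 10 (no unit or variable named), two-sided alpha 0.05, 44 per group, 6 dropouts per group. The beta of 0.80 is read as power 0.80; taken literally (20% power), the same two-means formula gives 7 per group. From the Introduction: 8%-10% edema at day 4, the figure nearest to the endpoint's time point. Allocation is 1:1.

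**1. Reproducing the 44 (two means, normal approximation).**
n = 2 × (1.960 + 0.842)² × SD² / difference² = 2 × 7.849 × 100 / 36 = 43.6, rounded up to 44.
Dropout: 44 + 6 = 50, and 44 / (1 − 0.12) = 50, which is consistent.
So the stated size is exactly a two-means calculation with difference 18 − 12 = 6 and SD 10.

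**2. The same rates as proportions.**
n = [1.960 × √(2 × 0.15 × 0.85) + 0.842 × √(0.18 × 0.82 + 0.12 × 0.88)]² / 0.06², which gives 555 per group (588 with continuity correction).
Power at 44 per group: the standard error is √(2 × 0.15 × 0.85 / 44) = 0.0761 under the null and √[(0.18 × 0.82 + 0.12 × 0.88) / 44] = 0.0759 under the alternative. Power = Φ[(0.06 − 1.960 × 0.0761) / 0.0759] = 12.0%. At 50 per group it is 13.1%.

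**3. Edema, if 8%-10% is mean percent swelling.**
Halving 8%-10% gives a difference of 4-5 points. The document names no edema SD, so the SDs below are assumptions. Power of the two-sided t test, alpha 0.05, 44 per arm:

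| Assumed edema SD (points) | Difference 4 | Difference 5 |
|---|---|---|
| 6 | 87% | 97% |
| 8 | 64% | 83% |
| 10 | 46% | 64% |
| 12 | 34% | 49% |

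The SD 10 row is 45.8% and 64.0%. With all 50 per arm evaluable it becomes 50.8% and 69.7%.
The effect detectable with 80% power at 44 per arm is 0.604 SD. So 80% requires an SD of at most 4 / 0.604 = 6.6 points (difference 4) or 5 / 0.604 = 8.3 points (difference 5).

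**4. Edema, if 8%-10% is the share of patients affected.**
With the formula of step 2 at 44 per group, 8% against 4% has 12.0% power and 10% against 5% has 14.1%.

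**The case against.** The strongest objection concerns the 46%-64%. Sigma 10 sits in a calculation on wound-complication figures and is tied to no edema measure. Borrowing it as the edema SD mixes two outcomes. This stands. A reader might infer that, on the protocol's own numbers, the trial has only about half to two thirds power for edema. The document does not support that: with an edema SD of 6 points power would be 87%-97%, and with SD 8 and a difference of 5 it would be 83%. The SD 10 row is one scenario.

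A second point is that both readings of 8%-10% need an assumption. The Introduction's wording suggests incidence, whereas edema is measured as leg circumference. The Abstract's wording could even mean a per-patient responder criterion, for which no expected rate is given. This also stands, and it adds to the case that the primary endpoint has no power basis.

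A third point is that a trial may be sized on an outcome other than its primary one. That does not rescue the paragraph, because step 2 shows that the calculation fails for wound complications too.

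Finally, a reader might infer that the department holds a series from which the edema SD can be read off. The Introduction says only that the figures are unpublished. It does not say whose they are or that an SD exists.

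**Conclusion.** The point holds in two parts, both certain from the text and simple arithmetic. First, the only power statement in the document does not address the declared primary endpoint. Second, it comes from treating two percentages as means. Compared as proportions they need about 555 per group, against the planned 44 evaluable, where power is about 12%. The quoted 80% is therefore established for neither outcome.

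How well the trial is powered for edema cannot be determined from the document. The 34%-97% range assumes that 8%-10% is mean percent swelling, that the target is half of it, and that the SD lies between 12 and 6 points. If 8%-10% is an incidence, power is about 12%-14%. The edema comparison may be adequately powered or badly underpowered, and the paragraph does not show which.

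This should be corrected, because the sample size rests on this figure alone.

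**What to change.** Remove the claim of 80% power for 18% versus 12%. Replace it with a calculation on the edema endpoint as the End points section defines it:

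- Cover both measuring sites, and reconcile the time point of three days after operation with the Day 4 measurement in the time schedule.
- Say whether edema is analysed as mean swelling, as the share of patients affected or as a per-patient response, and what the 8%-10% in the Introduction represents.
- State the assumed control mean, the planned difference, and the edema SD with its source. If no SD is available, give an explicit range, as in the table above.
- Report the power that 44 evaluable (50 randomised) per arm gives under those assumptions, and write power 0.80, not beta 0.80, wherever that value is meant.
- If wound complications stay in the paragraph, describe them as a further outcome for which the trial is not powered.

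The cost is one recalculation and a rewritten paragraph. Enrolment, treatment and visits are unchanged. The downside is that the stated power may become less favourable.

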### Statistical methods

Descriptive statistics will be used to report study results. For binary and categorical variables, tests of differences between the intervention and control group will be analyzed by the chi-square test. For continuous variables, initial tests will be performed to check for normality of data by using histograms, Q-Q plots and the Shapiro-Wilk test. Normally and nonnormally distributed variables will be analyzed by *t* test or the Wilcoxon rank sum test, respectively. *P* values <.05 will be considered statistically significant.

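### The 44 per arm reproduces from a formula for means, but 18% vs 12% wound complications is a binary contrast: power for it is about 12–14%, not 80%

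*Protocol article*

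**What the plan says.** The section Statistical Analysis and Structural Analysis holds the only sample-size reasoning in the protocol. It argues that halving the edema will lower wound complications: "we can reduce the wound complication rate for patients from 18% to 12%, given a sigma of 10 and the two-sided test". It continues "with an alpha value of 0.05 and beta of 0.80 involving 44 patients in each group", and then adds 6 dropouts per group to reach 50. The Sample size section repeats 50 per group, 100 in total.

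Under End points, wound complications are defined by the occurrence of infection, hematoma or lymph excretion, so each patient either has one or does not. The Statistical methods section says how such outcomes are tested: "For binary and categorical variables, tests of differences between the intervention and control group will be analyzed by the chi-square test".

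The Abstract (Results) names reduction of leg edema, not wound complications, as the primary endpoint, and the Introduction makes edema the primary objective.

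**The concern.** A comparison of two proportions has no free SD, because the rates themselves fix the variance. A calculation for 18% vs 12% that also needs a sigma of 10 therefore looks like a calculation for means, with percentage points treated as a continuous measurement. The stated sigma is also far too small for a yes/no outcome at these rates.

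The protocol presents 44 per arm as enough for 80% power on wound complications. If it is not, a null wound result could be read as adequately powered evidence of no effect, when the design would usually miss the very effect it assumes. In addition, beta is the type II error rate, so a beta of 0.80 taken literally means 20% power.

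**Working it through.** **Inputs, all from Statistical Analysis and Structural Analysis:** rates 18% and 12%; sigma 10, without a unit; two-sided alpha 0.05; 0.80 labelled beta; 44 evaluable per arm, 50 after adding 6 dropouts. The test (chi-square) comes from Statistical methods.

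**1. Reproducing the protocol's figure.** The two-means formula is n = 2(z₁₋α/₂ + z_power)² × SD² / difference². With difference 18 − 12 = 6 and SD 10:

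2 × (1.960 + 0.842)² × 100 / 36 = 43.6, so 44 per arm. Adding 6 gives 50.

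The match holds only if 0.80 is used as power. Taken literally as beta (power 0.20), the same formula gives 7 per arm, and the two-proportion formula gives 90.

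**2. Could a formula for proportions give 44?** No variant tried comes close. At 80% power for 18% vs 12%:

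| Variant | n per arm |
|---|---|
| Two-sided, no continuity correction | 555 |
| Two-sided, continuity correction | 588 |
| Two-sided, arcsine | 551 |
| One-sided, no continuity correction | 437 |
| One-sided, continuity correction | 470 |

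The first line is [1.960 × √(2 × 0.15 × 0.85) + 0.842 × √(0.18 × 0.82 + 0.12 × 0.88)]² / 0.06² = [1.960 × 0.5050 + 0.842 × 0.5032]² / 0.0036 ≈ 555.

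**3. The SD that the rates imply.** √(0.18 × 0.82) = 0.384 and √(0.12 × 0.88) = 0.325, that is about 38 and 32 percentage points per patient, against a stated 10.

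**4. Power at the planned size.** By normal approximation, power is Φ{[0.06 − 1.960 × √(2 × 0.15 × 0.85/n)] / √[(0.1476 + 0.1056)/n]}.

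- n = 44: (0.06 − 1.960 × 0.0761) / 0.0759 = −1.176, so 12.0%.
- n = 50: (0.06 − 1.960 × 0.0714) / 0.0712 = −1.124, so 13.1%.

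| Test, 18% vs 12% | 44 per arm | 50 per arm |
|---|---|---|
| Normal approximation, two-sided | 12.0% | 13.1% |
| Uncorrected chi-square, exact enumeration | 12.9% | 14.1% |
| Fisher's exact test | 7.2% | 7.8% |
| Normal approximation, one-sided | 19.5% | 21.0% |

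**5. What 44 per arm could detect.** For 80% power from a control rate of 18%, the pump rate would have to fall to about 0.8% by normal approximation. That approximation is poor at such small counts. Exact enumeration of the uncorrected chi-square test gives 80.6% power at 2%. The detectable fall is therefore from 18% to roughly 1–2%.

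**6. Expected precision.** The half-width of the 95% CI for the risk difference is 1.96 × √[(0.1476 + 0.1056)/n]: 14.9 points at 44 per arm and 13.9 at 50, around an assumed difference of 6 points.

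**The case against.** **The calculation is really about edema.** The sentence does begin with a halving of edema, and edema is the primary endpoint. But the only numeric contrast given is the wound complication rate, and the sigma is not tied to edema. The Introduction's approximate 6%–10% for edema comes from unpublished data and has no spread. Suppose those figures meant percent swelling, halved, with an SD of 10. The difference would be 3 to 5 points, and 2 × (1.960 + 0.842)² × 100 / difference² gives about 63 to 175 per arm, not 44. Of these contrasts, only the wound difference of 6 yields 44.

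**Wound complications are not primary, so low power is tolerable.** This stands as far as it goes. Low power on such an outcome can be acceptable, but a stated 80% that is really 12–14% is not. A reader might also infer that the trial as a whole has 12% power. The document does not support that: it gives no edema effect in measurement units and no edema SD, so power for the primary endpoint can be neither confirmed nor faulted.

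**The protocol names no formula.** True. Use of a means formula is inferred from the match at 44, the presence of a sigma, and the failure of every proportion variant tried. The power figures in steps 4 to 6 do not depend on that inference.

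**The groin wounds.** End points says "The pump is expected to have influence on the wounds on the thigh/crus and not in the groin". A reader might conclude that the overall difference must be smaller than 6 points. That goes too far. The documents do not say whether the 18% includes groin wounds or in what share, and the assumed 12% could already allow for an unaffected part. If groin wounds are included, the achievable overall difference may be smaller. The power result does not need this point.

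**Conclusion.** The sample-size statement is wrong as written. For its own contrast, tested as its own methods section provides, power is about 12–13% at 44 per arm and 13–14% at 50, against a stated 80%. The assumed effect would be missed in roughly 86–88% of repetitions, and the sample needed for 80% power is about 555/44 ≈ 12.6 times the stated number. A different choice of test does not rescue the claim: across those examined, power runs from about 7% to 21%. The beta label is a separate misstatement.

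This rests on taking 18% and 12% as per-patient rates of a binary outcome, two-sided alpha 0.05, 1:1 allocation, and 44 to 50 evaluable patients per arm. It is a conclusion about wound complications only.

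**What to change.** 1. Withdraw the claim that 44 (50) per arm gives 80% power for a fall from 18% to 12%, along with the sigma attached to it.
2. Replace the beta of 0.80 with power 0.80 (beta 0.20) wherever a power target remains.
3. Either state the true power for wound complications (about 12–14%), or label them a secondary, estimation-only outcome reported as a risk difference with a 95% CI. The expected half-width is about 15 points at 44 per arm and 14 at 50.
4. State what 100 patients deliver for the primary edema endpoint, using an explicit edema effect and SD in measurement units. The result should be reported as it falls; the document gives no ground for assuming in advance that it will support 100.

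The cost of items 1 to 3 is wording and a less favourable stated figure. Item 4 needs edema inputs that the sponsor must supply, and whether the number of patients stands depends on that calculation.

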## Abstract

**Background:**

In patients with critical leg ischemia (CLI), the standard operative choice is an in situ bypass to the lower extremity to improve the patients´ prognosis and quality of life. Postoperative complications after surgery occur in 18 % of the patients, prolonging hospitalization and convalescence. The main operative complication is edema. This can be prevented by early mobilization or stimulation of the natural venous pump in the leg.

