### Background and Rationale

In situ bypass to the lower extremity is the standard operation choice on patients with critical leg ischemia, accounting for approximately 18% of patients’ wound problems [11], prolonging their hospitalization time and convalescence. One of the reasons for wound problems is postoperative edemaThe edema is expected after open vascular reconstruction (in situ bypass surgery). Early mobilization can prevent development of the postoperative edema. Through mobilization, the patient stimulates the natural venous pump in the leg. However, patients are often hard to mobilize in an early stage due to the wound and age. Stimulation of the venous plexus in the arch of the foot has, in other categories of patients, shown to reduce postoperative edema of leg and thrombosis risk in patients undergoing orthopedic surgery on the lower extremities. The subjective quality of life is often impaired in relation to the above mentioned surgical treatment. Through a quicker recovery, the patient can rapidly regain mobility and walking capability.

There is no analysis or meta Cochrane reviews in this field.

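### The 18% behind the sample size is labelled as all postoperative complications in some sections and as wound complications in others, so the control wound rate is uncertain and the power must be restated as a comparison of two proportions

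*Protocol article*

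**What the plan says.** The protocol article uses 18% in four places.

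- **Abstract, Background:** "Postoperative complications after surgery occur in 18 % of the patients". Edema is then named as the main complication.
- **Introduction:** "postoperative complications after an in situ bypass occur in 18% of patients", followed by "The main postoperative complication is edema".
- **Background and Rationale:** in situ bypass is described as "accounting for approximately 18% of patients’ wound problems". This is the only use of the figure that carries a literature reference.
- **Statistical Analysis and Structural Analysis:** by halving edema "we can reduce the wound complication rate for patients from 18% to 12" per cent, so 18% is here the control wound-complication rate. The calculation is "given a sigma of 10 and the two-sided test", "with an alpha value of 0.05 and beta of 0.80", and arrives at 44 per group, raised to 50 for dropout.

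The End points section defines wound complications by the Danish vascular registry, "including infections, hematoma, and lymph excretion over two days". Edema is not in that list. Statistical methods assigns the chi-square test to binary variables.

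**The concern.** One figure stands for two different events. If 18% counts every patient with any postoperative complication, and edema is the commonest, then the rate of infection, hematoma and lymph excretion would be expected to be lower than 18%. If 18% is the wound rate, the Abstract and the Introduction describe it wrongly. The article gives no separate wound rate that would settle the matter.

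The control rate is a main input to any valid power statement for a binary endpoint. Someone who corrected the formula but carried the 18% over unchecked would still be relying on an input that the article contradicts. The planned 6-point fall is 18 minus 12, so its plausibility also depends on what the 18% counts.

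**Working it through.** **Inputs.** From Statistical Analysis and Structural Analysis: 18% and 12% (6 points, a relative reduction of 6/18 = one third), sigma 10, two-sided alpha 0.05, 44 per group, 6 dropouts per group. The stated beta of 0.80 is read as power 0.80. Read literally it would mean 20% power, and the same formula would then need only 7 per group.

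**Step 1: reproduce the plan's figure.** Formula for two means: n = 2(1.960 + 0.842)² × SD² / difference² = 2 × 7.849 × 100 / 36 = 43.6, so 44 per group. Adding 6 gives 50. The plan's figure is reproduced exactly. Only the difference of 6 and the SD of 10 enter. The 18% level does not, so relabelling it would leave 44 unchanged.

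**Step 2: treat the endpoint as binary.** Formula for two proportions with pooled variance under the null and mean rate 0.15:

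n = [1.960 × √(2 × 0.15 × 0.85) + 0.842 × √(0.18 × 0.82 + 0.12 × 0.88)]² / 0.06² = (0.990 + 0.424)² / 0.0036 ≈ 555 per arm.

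Exact power of the uncorrected chi-square test, summed over both binomial distributions, is 12.9% at 44 per arm and 14.1% at 50.

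**Step 3: let the control rate vary.** The article gives no other wound rate, so the rates below 18% are assumptions. The plan's one-third reduction is kept.

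| Control vs pump | Per arm for 80% power | Power at 44 | Power at 50 |
|---|---|---|---|
| 18% vs 12% (plan) | 555 | 13% | 14% |
| 15% vs 10% | 686 | 12% | 12% |
| 12% vs 8% | 882 | 11% | 10% |
| 10% vs 6.7% | about 1,080 | 10% | 9% |
| 9% vs 6% | 1,209 | 9% | 8% |
| 8% vs 5.3% | about 1,370 | 9% | 7% |

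In the lower rows the power at 50 falls below that at 44. This comes from the discreteness of the test at small counts: its actual size at a common rate of 8% is about 6.0% at 44 per arm and 4.7% at 50.

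**Step 4: check the direction.** Power falls with the control rate only if the relative reduction is held. With the 6-point difference held instead, exact power at 44 per arm rises to about 15% (15% vs 9%), 18% (12% vs 6%) and 25% (8% vs 2%). The last would be a reduction of three quarters. None of these comes near 80%.

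**The case against.** The strongest defence is that 18% is simply the wound rate. Background and Rationale ties it to wound problems and is the only section that cites a source for it, which agrees with the sample-size paragraph. The Abstract and the Introduction may just be using complications loosely. The definition in End points is also introduced as inclusive, so its list may not be complete. This stands to the extent that the article does not show 18% to be too high.

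A reader might infer more: that edema affects 8% to 10% of patients by day 4, that subtracting this from 18% leaves 8% to 10% for wounds, and that halving edema would spare only 4% to 5% of patients. The article does not support this. The Introduction's edema figures refer to the site where leg circumference is measured and may well be percentage swelling, not a share of patients. Background and Rationale says that edema is to be expected after this surgery, which fits poorly with an event in 8% to 10% of patients. That section and the Discussion also treat edema as a cause of wound complications, so one patient can have both and the two rates cannot be subtracted.

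It is also fair to say that little turns on the label alone. Power is about 13% with 18% and about 9% at the lowest assumed rate, and the primary endpoint is edema, not wounds. The inconsistency still needs correcting, because 18% is the only control event rate in the plan's sample-size argument.

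**Conclusion.** The point holds as an inconsistency in what the 18% counts, which leaves the control wound rate uncertain and possibly overstated. It does not hold as a demonstrated overstatement, and the label does not explain the stated 80%. That figure comes from applying a formula for two means to a binary endpoint.

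Even if 18% is correct, power for wound complications is about 13% at 44 and 14% at 50 per arm. Under assumed control rates of 8% to 15% it is about 9% to 12% at 44 and 7% to 12% at 50. These figures assume a two-sided uncorrected chi-square test at 0.05 and the plan's one-third relative reduction. The 8% to 15% range is illustrative and is not derived from the article.

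**What to change.** 1. Make the Abstract, the Introduction, Background and Rationale, and Statistical Analysis and Structural Analysis agree on which event the 18% counts.
2. Confirm the control rate of wound complications as End points defines them, for example from the karbase registry which that section already names. Use that rate in the sample-size paragraph, whether or not it turns out to be 18%.
3. Keep 50 per arm and restate the power for this binary endpoint with a two-proportion (chi-square) calculation, writing power where the text now says beta.

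The cost is a registry look-up, some rewording, and a stated power for wound complications far below 80%. No extra patients are needed.

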## Methods

The trial design is a 1:1 randomized prospective study. All surgical procedures will be performed by vascular surgeons. The postoperative care will be performed by special nurses in cooperation with vascular surgeons at the Department of Vascular Surgery, Lillebaelt Hospital, Denmark.

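### The sample-size sentence labels 0.80 as beta, but its 44 per group follows only from a power of 0.80; a minor labelling error that leaves 44 and 50 unchanged

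*Protocol article*

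**What the plan says.** The calculation is in the protocol article under Statistical Analysis and Structural Analysis. It starts from the expectation that, by halving edema, "we can reduce the wound complication rate for patients from 18% to 12" per cent. It then sets the remaining inputs, "given a sigma of 10 and the two-sided test", and concludes "with an alpha value of 0.05 and beta of 0.80 involving 44 patients in each group". An allowance follows, "Assuming a dropout rate of 6 patients in each group", which brings each group to 50.

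The Sample size section gives only the result: "The sample will comprise of 50 patients in each group with a total of 100 patients". It mentions neither beta nor power. No other section states the power, defines beta differently or corrects the value. Statistical methods adds the significance threshold and the tests, including a chi-square test for binary variables.

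**The concern.** By definition beta is the probability of missing the planned effect, and power is 1 − beta. A beta of 0.80 therefore means power of 0.20. If 44 per group was computed for power 0.80, the printed beta and the printed sample size cannot both be right.

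What is at stake is whether the design can be reproduced and reported correctly. This is the protocol's one statement of the error rates behind its size. A reader who enters the printed inputs literally does not get the printed answer.

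**Working it through.** **Inputs**, all from Statistical Analysis and Structural Analysis except the allocation ratio:
- alpha 0.05, two-sided
- difference 18 − 12 = 6
- sigma 10
- 44 per group before dropout, with 6 dropouts per group
- allocation 1:1 (Methods)

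The article does not name its formula. Because it prints a sigma, the comparison of two means is the natural one to try.

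**Formula:** n per group = 2 × (z₀.₉₇₅ + z_power)² × sigma² / difference²

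**Reproducing the plan's figure, power 0.80 (beta 0.20):**
2 × (1.960 + 0.842)² × 100 / 36 = 43.6, rounded up to **44**. This matches the printed number.

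**Taking beta 0.80 literally (power 0.20):**
2 × (1.960 − 0.842)² × 100 / 36 = 6.95, rounded up to **7**. This does not match.

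**Check in reverse:** with 44 per group the standard error is 10 × √(2/44) = 2.132. Then 6/2.132 − 1.960 = 0.854, which is a power of 0.804 (0.795 by the t distribution). So 44 per group corresponds to beta of about 0.20.

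**Could another method reconcile beta 0.80 with 44?** Results per group:

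| Method | Power 0.80 | Power 0.20 |
|---|---|---|
| Two means, two-sided, normal | 44 | 7 |
| Two means, two-sided, t | 45 | 8 |
| Two means, one-sided | 35 | 4 |
| Two proportions, two-sided | 555 | 90 |
| Two proportions, two-sided, continuity correction | 588 | 121 |
| Two proportions, one-sided | 437 | 47 |
| Two proportions, one-sided, continuity correction | 470 | 76 |

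No entry at power 0.20 equals 44. The nearest, 47, needs a one-sided test, which the article rules out, and makes no use of the printed sigma. Only the two-sided two-means formula at power 0.80 gives exactly 44.

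**Dropout:** 44 + 6 = 50, or equally 44 / (1 − 6/50) = 50. Correcting the label changes neither number.

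**What the corrected 0.80 covers:** it holds for a difference of 6 in a continuous measure with standard deviation 10. For two proportions, 0.18 and 0.12 (mean 0.15), at 44 per group:
- standard error under no difference: √(2 × 0.15 × 0.85 / 44) = 0.0761
- standard error under the planned difference: √((0.18 × 0.82 + 0.12 × 0.88) / 44) = 0.0759
- power = Φ((0.06 − 1.960 × 0.0761) / 0.0759) = Φ(−1.18) = **0.12**

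The same calculation at 50 per group gives **0.13**.

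**The case against.** The strongest reply is that this is a slip of vocabulary with no effect on the trial. A statistician will guess that 0.80 is the power, the 44 already uses it, and patients, schedule and analysis stay as they are. That stands, and it is why the point is minor. It does not make the printed value right: the error is in the sentence that justifies the trial's size, and nothing else in the article corrects it.

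A second reply is that the figure of 7 appears only after adopting a formula the article never names, and one that does not suit the binary outcome in the sentence. That is fair as far as it goes. The formula is an inference, but the printed sigma points to it and it returns 44 exactly.

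A third reply is that relabelling alone could mislead, because the sentence would then appear to claim 80% power for wound complications. This stands in full, and the correction has to deal with it.

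A reader might also infer that the trial was planned with one chance in five of detecting its effect. The printed 44 rules that out under the formula that produces it. Nor is the Sample size section a second instance of the error, since it gives only 50 per group and 100 in total.

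**Conclusion.** The point holds as a minor correction. The printed beta of 0.80 is the power, mislabelled: the type II error that yields 44 is 0.20, a quarter of the one stated. This rests on the two-means formula with difference 6, sigma 10 and two-sided alpha 0.05.

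Two stronger conclusions might be drawn, and the document supports neither. The first is that the mislabelling calls for a different sample size; it does not, because 44 and 50 per group follow unchanged once the label is right. The second runs the other way: that correcting the label confirms 80% power to detect a fall in wound complications from 18% to 12%. It does not, because for that binary comparison the power is about 12% at 44 per group. Whether a continuous-outcome formula should have been used for a complication rate is a separate and more serious question. Here it only limits what the corrected figure may be said to apply to.

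**What to change.** In Statistical Analysis and Structural Analysis, replace the reference to a beta of 0.80 with *power of 0.80 (beta of 0.20)*. In the same place, state that this power applies to a difference of 6 in a continuous measure with a standard deviation of 10, and do not present it as the power for the wound complication rate of 18% versus 12%.

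The Sample size section needs no edit. The cost is one corrected phrase and one clarifying clause, with no change to patient numbers, schedule or analysis.
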